### Sample size

The sample size for the RCT was calculated to detect a minimally important difference (MID) in the primary outcome measure (PCS-12). The developers suggest that the MID for interpretation of group mean PCS-12 score differences is approximately 3.0, which corresponds to an effect size of 0.30 [56]. However, the developers also acknowledge that this MID estimate is a matter of ongoing debate. Robust research on effect sizes seen across a range of studies using a variety of quality-of-life measures has shown that the mean effect size is remarkably consistent at 0.50, or half the standard deviation [57]. This effect size is close to the one observed in our pilot study, which was 0.40 [43].

We based our estimate of the sample size on an effect size of 0.50, 5% alpha, 80% power and 20% attrition (18% was observed in our pilot study). Using these assumptions, the sample size was 80 (each) for the intervention and control groups.

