### Randomization design

After providing written, informed consent and completing the baseline questionnaires, participants will be randomly assigned to either the intervention or the control arm of the study using a 1:1 allocation ratio. Stratified permuted block randomization will be used to assign participants to the control and intervention groups. Study sites are expected to be relatively homogeneous regarding client sociodemographic and clinical characteristics and the delivery of intervention and usual care services. However, to minimize the confounding effects of possible differences among the study sites, the sites will be used as a stratum. The randomized sequence at each site will be based on assignments of blocks randomly selected from sizes of 2, 4, or 6. A biostatistician not involved in the recruitment process will generate the random number assignments for each site using SAS Version 9.3. Random number sequences will be input into a centralized web-based randomization service (REDCap) that will allocate clients to the control or intervention group at each site in accordance with the sequence.

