### Analyses

#### Analysis of participants

The data collected will be screened for accuracy, missing data, outliers, and statistical assumptions. SAS Version 9.3 will be used for all statistical analyses. All statistical tests will be performed using two-sided tests at the 0.05 significance level. For all models, the results will be expressed as effects, standard errors, 95% confidence intervals, and associated *p* values. The evaluation will be conducted in accordance with the intention-to-treat principle; therefore, imputation (using multiple imputation) will be used to address missing data and compare these results with the complete case analysis. If there are discrepancies between the multiple imputation and complete case results, we will conduct a sensitivity analysis using different multiple imputation methods (appropriate for the pattern of missingness) to see how robust the analysis is for the chosen method(s) of handling missing data [85]. This procedure will result in multiple data sets and models being run on each data set. Appropriate methods will be used to combine the results to generate pooled parameter estimates, standard errors, and confidence limits.

An analysis of baseline (*T*1) data will be performed to compare the demographic and clinical characteristics of the intervention and control groups. This analysis will confirm whether the two groups are equal on these variables. Means and standard deviations will be generated for continuous variables, and frequencies and proportions for categorical variables. The appropriate significance test (e.g., *t* test for continuous measures, chi-square for categorical) will be applied to identify any significant differences between the groups. Significant differences will be adjusted for in the outcomes analyses.

For the analyses relating to clients, *t* tests will be used to compare the changes in primary and secondary outcomes from baseline (*T*
_1_) and 6 months (*T*

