_2_) in the two groups. Primary and secondary measures will also be analyzed using repeated measures ANCOVA (two time periods) to understand the factors shaping these outcomes. Site will be included as a predictor, consistent with our randomization strategy which stratified by site. Other potential covariates include age, gender, self-efficacy, duration of diabetes, and level of comorbidity. Covariates will be identified and selected for inclusion in the models based on bivariate analyses to confirm their relationship with the outcome and the absence of a significant relationship with other covariates. We will conduct a cross-jurisdictional comparison across Ontario and Alberta, given the differences in community-based structures.

We will also examine the relationship between the dose of the intervention and the primary outcome variable (6-month PCS-12 score) in order to better understand the mechanisms underlying this outcome and to tease out quantity versus quality effects. Regression will be used and dose will be measured by the number of home visits and number of group sessions attended (explored as individual components and as a combined measure).

The effectiveness of an intervention is often dependent on the characteristics of the population; thus, this study will include a subgroup analysis to identify what clients benefit most from which approach to treatment [86]. A range of characteristics thought to influence self-management behavior will be evaluated, including: age, gender, duration of diabetes, depressive symptoms, number of comorbidities, self-efficacy and caregiver support. Regression using two-way interactions between the study group (intervention versus control) and each characteristic will be conducted to examine subgroup effects [87, 88]. The models will use the PCS-12 score for the dependent variable and independent variables will include group assignment, client characteristic (e.g., at least three versus less than three comorbidities), and the interaction term.

Regarding the family caregivers, data on their demographic characteristics and the three outcomes (HRQoL, depressive symptoms, and strain) will be collected at baseline and again at 6 months. Descriptive statistics will be generated to summarize the characteristics and outcomes for the family caregivers in each group, with *t* tests and chi-square tests being used to evaluate group differences in continuous and categorical variables, respectively.

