## Discussion

This paper describes the design of a multisite, two-arm, pragmatic, mixed-methods RCT of the effectiveness of the ACHRU-CPP aimed at improving self-management in older adults with T2DM and MCC and providing support to caregivers. This research makes several important contributions to the existing knowledge base. First, it investigates the effectiveness of a self-management intervention in a complex population. This population is particularly at risk of adverse outcomes, yet they are often excluded from RCTs. As a result, their needs are poorly understood and evidence of the effectiveness of interventions aimed at behavioral change in this vulnerable group is lacking. The exclusion of this group is important; about 60% of older adults with T2DM have at least one comorbid condition and 40% have three or more [8–10]. Second, the study includes a subgroup analysis to determine which study clients benefit most from the program. Few intervention studies conduct this type of analysis, yet it is critical for informing the implementation of the program in other settings and to target scarce resources to those most likely to benefit [86]. Third, the study includes a cost analysis, which provides policy-makers with critical information on the resource implications of the program to facilitate decision-making.

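### At least seven unadjusted interaction tests with low power cannot determine who benefits most, and the one coding example given discards information

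*Protocol article*

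**What the plan says.** The second of the four aims in the Objectives section is to determine which subgroups of older adults gain most from the program. The opening paragraph of the Discussion calls this analysis critical for implementation elsewhere and gives its use as "to target scarce resources to those most likely to benefit".

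The method is in Analysis of participants. The characteristics are "age, gender, duration of diabetes, depressive symptoms, number of comorbidities, self-efficacy and caregiver support", introduced as included in a range, so seven is a minimum. The test is stated as "Regression using two-way interactions between the study group (intervention versus control) and each characteristic will be conducted to examine subgroup effects", with PCS-12 as the dependent variable. The only coding shown for a characteristic is a parenthetical example: "at least three versus less than three comorbidities". The inclusion criteria require at least two chronic conditions besides T2DM.

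The error rate is set at the start of the same section: "All statistical tests will be performed using two-sided tests at the 0.05 significance level". Nothing exempts the subgroup tests from this, and they are not labelled exploratory. Other analyses are. Table 2 describes the ANCOVA and the dose regression as exploring, and the interventionist paragraph uses the same verb and admits its small numbers.

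The Sample size section covers the main effect on PCS-12 only: "We based our estimate of the sample size on an effect size of 0.50, 5% alpha, 80% power and 20% attrition".

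**The concern.** The article promises a determination of who benefits and names a use for it, resource allocation. The analysis behind that promise is a family of at least seven tests, each at an unadjusted 0.05, in a trial sized for one main effect. Such a family has a material chance of producing a significant interaction when none exists, and a poor chance of finding one that does exist. The stated aim therefore claims more than the design can deliver.

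A second, smaller problem is the illustrated coding. Number of comorbidities is collected as a count. Because eligibility sets a floor of two, the lower category of the example can hold only clients with exactly two conditions, while clients with three, five or eight are treated alike. If the models follow the example, tests that are already weak lose more information.

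**Working it through.** **1. The plan's own sample size.** Inputs from Sample size: effect size 0.50, two-sided alpha 0.05, power 80%, attrition 20%.
- Normal approximation: n per arm = 2 × (1.960 + 0.842)² / 0.50² = 62.8, rounded up to 63; 63 / 0.80 = 78.75, rounded up to 79.
- t-based: 64 per arm; 64 / 0.80 = 80.

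The plan states that "the sample size was 80 (each) for the intervention and control groups", so its figure reproduces for the main effect. Expected completers are 160 × 0.80 = 128. Participants and setting instead gives 160 in each province, against 160 in total in the Abstract. On that reading, completers are 320 × 0.80 = 256. Both are carried below.

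**2. False positives.** Seven tests at 0.05, all nulls true:
- independent tests: 1 − 0.95⁷ = 0.302;
- bound under any dependence: 7 × 0.05 = 0.35.

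More than seven characteristics would raise both figures.

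**3. Power for an interaction.** Allocation is made "using a 1:1 allocation ratio". For a two-category moderator with share p in the smaller category and N analysed, in outcome SD units:

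SE = √[(4/N) × (1/p + 1/(1 − p))]

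Power for a difference in effect of 0.50 SD = Φ(0.50/SE − 1.96) + Φ(−0.50/SE − 1.96)

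| N | Split | SE | Power for 0.50 SD |
|---|---|---|---|
| 128 | 50/50 | 0.354 | 29% |
| 128 | 33/67 | 0.375 | 27% |
| 256 | 50/50 | 0.250 | 52% |
| 256 | 33/67 | 0.265 | 47% |

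A slightly different method gives 28.9% and 26.3% for the two rows at N = 128, hence a range of about 26–29%. At N = 128 and 50/50, the interaction detectable with 80% power is (1.960 + 0.842) × 0.354 = 0.99 SD, twice the design effect. A 0.50 SD interaction would need about 503 analysed: 16 × (2.802/0.50)² = 502.3.

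**4. Where the 33/67 split comes from.** The Discussion says about 60% of older adults with T2DM have at least one comorbid condition and 40% have three or more. That leaves 20 points for one or two conditions together. Among those with at least two, the share with exactly two is largest if nobody has exactly one: 20/60 = one third, or about 43 of 128. This assumes that the cited population figures apply to those enrolled.

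**5. Cost of the cut.** For a normal moderator cut at a point with share p on one side, the information kept is φ(z)² / [p(1 − p)].
- At p = 1/3: z = 0.431 and φ(z) = 0.364, so 0.364² / 0.222 is about 0.60. About 40% is lost.
- At p = 1/2: 0.637 is kept.
- For a count distributed as 2 + Poisson(1.1), with 67% at three or more: about 0.55 is kept.

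At 0.595, a linear interaction with 80% power when modelled continuously falls to Φ(2.802 × √0.595 − 1.96) = Φ(0.20), about 58%. The distributions are assumptions; the article gives none for the sample.

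**The case against.** The strongest reply is that this is a condensed article. The characteristics are named in advance, interaction tests are used rather than separate tests within subgroups, and effects with 95% confidence intervals are already promised for all models. Multiplicity rules and moderator coding are often left to the analysis plan. All of that is fair, and the use of interaction tests should stay. But the article does not leave the matter open: it sets 0.05 for all tests and states the aim as determining who benefits, while reserving exploratory language for other analyses. A later exploratory label would conflict with the published objective.

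Three stronger readings are tempting and are not supported.
- A reader might infer that the cut at three contradicts eligibility. It does not. With a floor of two, both categories can be filled, and three or more is also the level the article uses to describe disease burden.
- A reader might infer that age, diabetes duration, depressive symptoms and self-efficacy will be dichotomised too. No cut is stated for any of them, and the comorbidity cut is itself only an example.
- A reader might infer that any subgroup announced is probably a false positive. The 30% is the chance of at least one false positive when every null is true. The probability that a given positive is false needs a prior that the documents do not supply.

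It is also true that low interaction power is usual in a trial sized on its main effect, that multiple imputation is planned, and that a real threshold effect would favour a cut. None of this rescues the stated aim. Even if all 160 clients contributed full information, SE at 50/50 would be √(16/160) = 0.316 and power about 35%.

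**Conclusion.** The point holds in two parts of unequal weight.

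The main part is that at least seven unadjusted interaction tests cannot support a claim to have determined who benefits most. The family-wise error and power figures in the working show this under either enrolment reading. They rest on all nulls being true (for the error rate), on two-category moderators with equal variances (for power), and on assumed splits. Resolving the enrolment total changes the size of the power shortfall but does not remove it.

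The lesser part is that the illustrated coding throws away count information that the trial will hold. The loss of about 40% is conditional on a roughly normal moderator and a 67/33 split. It is a poor example rather than an error or a binding rule.

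The single primary comparison of PCS-12 is untouched by either part. What is affected is Objective 2 and the resource-targeting use that the Discussion attaches to it.

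**What to change.** In Analysis of participants, replace the comorbidity example with number of comorbidities entered as a count. State that age, diabetes duration, baseline depressive symptoms and baseline self-efficacy enter as continuous terms interacted with group, with a check of linearity. Use cut-points only to display results. Keep the interaction tests and the planned confidence intervals, and report every interaction examined.

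In Objectives, Analysis of participants and the Discussion, reword the aim from determining or identifying who benefits most to exploring it. State that no subgroup will be declared to benefit most on an unadjusted p < 0.05.

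This needs no new data or visits. The cost is a more modest subgroup claim and a linearity assumption to check.

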#### Analysis of clinical effectiveness

##### Outcome measures

Table 2 describes the primary and secondary outcome measures used to evaluate clinical effectiveness. The primary outcome is the change in Physical Component Summary (PCS-12) score from the short form-12v2 health survey (SF-12) [58]. The SF-12 is a generic quality-of-life instrument that is well-validated and able to distinguish between groups of clients with known clinical differences in a variety of populations [58]. The pilot study supported the selection of the PCS-12 score as the primary outcome by demonstrating that the PCS-12 was responsive over the 6-month intervention period and grounded in questions that were easily interpreted by the older adult clients [43]. The PCS-12 is also a common primary outcome in studies evaluating programs similar to ours [59] and focuses on an outcome (physical functional ability) that is important to clients [60]. Secondary outcomes include the change in the following variables from baseline (*T*
_1_) to 6 months (*T*
_2_): Mental Component Summary (MCS) score from SF-12 [61]; Center for Epidemiological Studies Depression Scale (CES-D-10) [62–65]; Generalized Anxiety Disorder 7-item scale (GAD-7) [66–70]; Summary of Diabetes Self Care Activities (SDSCA) [71, 72]; and the Modified Caregiver Strain Index (CSI) [73].

**Table 2 Tab2:** Effectiveness outcomes, target population, and analysis

Effectiveness outcomes				
Variable/outcome	Hypothesis	Measure	Group(s)^a^	Method of analysis
Physical functioning	Improve more in the intervention group	Physical Component Summary (PCS-12) [58]	CT, CG	Means and standard deviations, *t* tests for comparing change from baseline (*T* _1_) to 6 months (*T* _2_) in the intervention and control groups ANCOVA analysis to explore predictors of primary outcome multiple regression with backward selection to explore impact of dose on primary outcome
Mental functioning	Improve more in the intervention group	Mental Component Summary (MCS) from SF-12 [61]	CT, CG	
Depressive symptoms	Larger reduction in the intervention group	Center for Epidemiological Studies Depression Scale (CES-D-10) [62–65]	CT, CG	
Anxiety	Larger reduction in the intervention group	Generalized Anxiety Disorder 7-item Scale (GAD-7) [66–70]	CT	
Self-management	More improvement in the intervention group	Summary of Diabetes Self Care Activities (SDSCA) [71, 72]	CT	

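### Caregiver outcomes are compared by change-score t tests; baseline-adjusted ANCOVA would answer Objective 3 more precisely from data already collected

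*Protocol article*

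**What the plan says.** The article's Objectives section lists, as its third objective, a comparison of the intervention with usual care on caregivers' health-related quality of life, strain, depressive symptoms and service costs. Under Analysis of participants, "the three outcomes (HRQoL, depressive symptoms, and strain) will be collected at baseline and again at 6 months". The same paragraph plans descriptive summaries by group, with *t* "tests and chi-square tests being used to evaluate group differences". It names no covariate and does not say whether the t test is on change or on the 6-month score.

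Table 2 (Outcome measures) fills that gap. Its PCS-12 row is marked for clients and caregivers, and the method cell beside it gives t tests on change from baseline to 6 months. The cell is empty for the rows below, so it appears to cover MCS, CES-D-10 and the caregiver strain index too. The same cell mentions ANCOVA only as "ANCOVA analysis to explore predictors of primary outcome".

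Three other statements bear on the point:
- Randomization design: "the sites will be used as a stratum".
- The client paragraph of Analysis of participants: "Site will be included as a predictor, consistent with our randomization strategy which stratified by site".
- The baseline-comparison paragraph of the same section: "Significant differences will be adjusted for in the outcomes analyses".

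**The concern.** The comparison is a numbered objective with directional hypotheses in Table 2, and the baseline value of every caregiver outcome will be in hand. The plan uses that value in a fixed way, by subtraction. That is the most efficient use only if the baseline-to-6-month correlation is 1. At any lower correlation it adds noise, and it over-corrects when the arms differ at baseline by chance.

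This matters more for caregivers than for clients. The section Screening for eligibility and enrolment makes caregiver participation optional, so the caregiver sample may be well below the client sample. The article states no power for it. What is at stake is a wider confidence interval than the data require, on a comparison that may already be small.

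**Working it through.** **1. The plan's own figure.** The Sample size section gives 80 clients per arm from an effect size of 0.50, two-sided 5% alpha, 80% power and 20% attrition. Normal approximation: 2 × (1.960 + 0.842)² / 0.50² = 62.8, so 63 per arm, and 63/0.8 = 78.75, so 79. The exact t test needs 64, and 64/0.8 = 80. The figure reproduces. It applies to clients; none is given for caregivers.

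**2. Inputs for caregivers.**
- From the article: 1:1 allocation, two-sided 5% tests, and the 0.50 SD effect size, borrowed from the client calculation.
- Assumed, because the article gives neither: 30 caregivers per arm with 6-month data, and correlation rho of 0.3, 0.5 or 0.7 between baseline and 6 months. Equal SDs at the two times are also assumed.

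**3. Variance of the group difference, in units of 2σ²/n.**
- t test on the 6-month score: 1
- t test on change: 2(1 − rho)
- ANCOVA on baseline: 1 − rho²

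The ratio of ANCOVA to change is (1 − rho²) / [2(1 − rho)] = (1 + rho)/2, which is below 1 for every rho below 1.

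**4. Power.** Noncentral t, with noncentrality 0.5 / √(2v/30), where v is the variance factor. Degrees of freedom are 58 for the t tests and 57 for ANCOVA. As an example, at rho = 0.5 the noncentrality is 0.5/√(2 × 1/30) = 1.94 for change and 0.5/√(2 × 0.75/30) = 2.24 for ANCOVA.

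| rho | v, change | v, ANCOVA | ANCOVA/change | Power, change | Power, ANCOVA |
|---|---|---|---|---|---|
| 0.3 | 1.40 | 0.91 | 65% | 36% | 51% |
| 0.5 | 1.00 | 0.75 | 75% | 48% | 59% |
| 0.7 | 0.60 | 0.51 | 85% | 69% | 76% |

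The interval width shrinks by about the square root of the ratio: √0.65 = 0.81, √0.75 = 0.87, √0.85 = 0.92. If the caregiver paragraph means a t test on the 6-month score instead, v is 1 and power is 48% at every rho.

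**5. Site.** In a simulation with seven sites, 25 caregivers per arm and rho = 0.5, the mean standard error was 0.281 for the change-score test, 0.246 for ANCOVA without site and 0.247 to 0.248 with site. The gain comes from the baseline value. Site neither adds precision nor costs much.

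**6. Whether another provision secures the gain.** The repeated measures ANCOVA over two time periods is described in the client paragraph. Even if it were extended to caregivers, its group-by-time test with two time points is the change-score test. The rule on significant baseline differences acts only after a positive baseline test, and that baseline analysis is described as a comparison of demographic and clinical characteristics. Neither commits the plan to baseline-adjusted caregiver outcomes.

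**The case against.** The strongest reply is that nothing here is invalid. A t test in a randomised comparison is unbiased, the caregiver outcomes are secondary, and a condensed article may leave covariates to an analysis plan. The first two parts stand and limit the point to efficiency. The third carries less weight because the article does name the caregiver method, so this is a stated choice and not a gap.

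A reader might infer several stronger things that the documents do not support:
- *The baseline is ignored.* Table 2 indicates change scores, so the baseline is subtracted. It is not modelled as a covariate.
- *The loss is as large as against a 6-month-score test* (ANCOVA variance 91%, 75% or 51% of that test's). Those ratios apply only if the caregiver paragraph departs from Table 2.
- *Omitting site throws away precision.* The simulation shows almost no effect. The case for site is consistency with the stratified design and the client model.
- *Clients get a properly adjusted main comparison and caregivers do not.* The client comparison is also by t tests on change. The client ANCOVA is there to understand what shapes the outcomes. The real difference is that clients have a model with a site term.
- *Chance imbalance has no remedy at all.* The conditional rule exists and could reach caregivers, but it depends on the data and prespecifies nothing.

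It can also be said that the caregiver analysis is mainly descriptive. The sentence does start with descriptive statistics and covers characteristics as well as outcomes, but it goes on to plan significance tests between the groups.

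**Conclusion.** The point holds as an efficiency weakness in secondary outcomes. On the change-score reading, ANCOVA would cut the variance of the caregiver comparison by 35%, 25% or 15% at a correlation of 0.3, 0.5 or 0.7. With 30 caregivers per arm and a 0.5 SD effect, that is worth about 15, 11 or 7 percentage points of power (51 − 36, 59 − 48, 76 − 69). The direction is certain for any correlation below 1. The size rests on the assumed correlation, caregiver number and equal SDs, and shrinks as the correlation rises. Bias or an invalid test should not be inferred: under randomisation the planned t test estimates the same difference, less precisely. The change is worth making because it costs nothing, but the trial's main conclusion does not depend on it.

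**What to change.** In the caregiver paragraph of Analysis of participants and in Table 2, prespecify for each caregiver outcome (PCS-12, MCS, CES-D-10 and the caregiver strain index) an ANCOVA of the 6-month score on group and that outcome's baseline value. Include site, or province if some sites have few caregivers, to match the stratified randomisation and the client model. Report the adjusted difference with its 95% confidence interval, and keep the t test as a supporting unadjusted result, stating that it is on change. Make the adjustment unconditional, so that it does not hang on a baseline significance test. The cost is a few lines of wording, with no new data, visits or participants.
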